#### Exclusion criteria

People ineligible to take part will be those:

• Receiving an ATT intervention already (excluding the sole provision of smoke, carbon monoxide or pendant alarms) or where ATT has previously been provided but has not been used;

• Being unlikely to comply with follow-up, e.g. because of an unstable medical condition;

• Participating in another clinical trial involving an intervention for dementia;

• Having an urgent need for a care package due to immediate and severe risks to themselves or others.

### Recruitment/consent procedures

There will be several routes for participant recruitment. NHS services (mental health or otherwise) will likely be the first-line sources for recruitment. We will extend recruitment beyond the NHS to local social services and include all people with dementia assessed through the FACS processes (as did the WSD)
[23]. Those referred from the NHS will have to meet FACS eligibility and those referred via CASSRs will either have a diagnosis of dementia or evidence of severe memory impairment.

Participating CASSRs will, after assessing FACS eligibility, ask all FACS-eligible referrals who may meet the other ATTILA trial eligibility criteria if their contact details can be made available to a named individual in a local ATTILA research team. Once identified, they will be registered with the ATTILA Study Office. A member of the local research team will contact this person and recruit them according to the trial standard operating procedures, followed by the appropriate randomisation procedures.

Consent will be sought using a defined protocol that meets the requirements of England’s Mental Capacity Act (2005), and where appropriate, data sharing agreements will previously have been agreed with the CASSR concerned to ensure that the transfer of personal data from the CASSR to the research team is lawful. If consent is not given, the individual will not be recruited and all of their personal data will be removed from research team records and destroyed.

For FACS-eligible participants who come from CASSRs, referrers will contact the local ATTILA study centres, which will arrange for a researcher to visit the prospective participant to explain the study and check eligibility to take part in the trial. If there is an urgent need for community or other forms of care or support services, then consent will be sought at that visit so that the prospective participant can be immediately randomised. If an urgent need for social services is not apparent, then information about the study will be left with the prospective participant and the researcher will return 24 h later to obtain consent to participate in the study. The participant will then be randomised. After randomisation, assessment for ATT and for provision of ATT services (within limits set by randomisation) will be left entirely to the local social services authority concerned. Participants who come from the NHS will only be eligible once FACS eligibility has been established by the CASSR.

### Assessments

Assessments will be undertaken by local investigators employed by the ATTILA team in weeks 0 (baseline), 12, 24, 52 and 104. All local investigators are researchers with clinical experience.

Following an assessment of mental capacity (and therefore ability to consent), confirmation of eligibility to take part, the consent process and randomisation, both groups will receive an initial assessment using the following scales: the Bristol Activities of Daily Living Scale (BADLS)
[29], Standardised Mini-mental State Exam (SMMSE)
[30,31], the Client Services Receipt Inventory (CSRI)
[32], The Model of Human Occupation Screening Tool (MOHOST)
[33] and the EuroQol EQ-5D
[34]. Unpaid carers of participants will be assessed over the same intervals using the Zarit Burden Inventory (ZBI)
[35], The Centre for Epidemiological Studies Depression Scale (CES-D10)
[36], the State Trait Anxiety Inventory (STAI-6)
[37], the Short Form Health Survey (SF-12v2)
[38] and the Carer Technology Acceptance Questionnaire (SUTAQ)
[39]. All of the outcome measures have established validity and high levels of inter- and intra-rater reliability. No pre-testing before randomisation is possible because of concerns by local authority hosts that this will delay the deployment of care and/or telecare to people who may have urgent needs for support.

### Primary outcome measures

#### Time in days from randomisation to institutionalisation

This is defined as the permanent transition of the individual from living in their own home to nursing or residential care home or to admission to an acute care facility that results in permanent placement in a residential care or nursing home.

#### Cost-effectiveness

Costs will be calculated by attaching nationally applicable unit cost measures to health and social service use (collected at intervals stated above for each participant using a modified version of the CSRI), using national figures taken from the Personal Social Services Research Unit (PSSRU) annual compendium
[40] where available. The costs of ATT will be calculated anew for those services provided, and in this we will be guided by methods and experience gained in the WSD trial of telecare and telehealth
[25]. *Data on carer time and task inputs* will come from the CSRI, and will be valued using two approaches (replacement wage and opportunity cost) and then comparing the results in sensitivity analyses.

*Cost-effectiveness analyses* will be of two types to take into account the complication that the primary outcome (time to institutionalisation) is itself partly an indicator of resource use. Each type of analysis will then be conducted from each of two perspectives: for the ‘formal’ health and social care system (which is, for example, the perspective employed by the National Institute for Health and Care Excellence in England and Wales to appraise health technologies as a basis for producing clinical guidelines
[41]) and for society as a whole (which would then additionally include the value of carer time and any productivity losses from disrupted employment, either for the person with dementia or the carer).

The first type of cost-effectiveness analysis will measure costs only up to the point at which a study participant goes into a care home or hospital and not beyond (‘community costs’) and will then examine cost-effectiveness in achieving the primary outcome (days from randomisation to institutionalisation in the two year period). This analysis will show the incremental cost of community-based support for each additional institutional day avoided. The second type of analysis will measure costs for the whole 2-year period, including costs of care home and hospital stays (‘total costs’), and will then examine cost-effectiveness where the outcome is EQ-5D change, also over the 2-year period. We will also use the EQ-5D to generate Quality-Adjusted Life Year (QALY) measures by attaching societal weights
[42].

We will compute incremental cost-effectiveness ratios and plot cost-effectiveness acceptability curves, which will be generated from the net benefit approach and using bootstrap regression for a range of values of willingness to pay for the corresponding outcomes. In each case, we will also be able to carry out these analyses at 24 and 52 weeks.

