[6-10] and to save CASSRs money. By addressing risks associated with independent living for people with dementia, ATT has claimed to help reduce the need for community care, prevent unnecessary hospital admissions, and delay or prevent admission into residential or nursing care.
[7,11-13] The evidence to support such claims is limited and based largely on qualitative evidence or uncontrolled quantitative studies
[14,15]. There is, therefore, an urgent need to provide evidence to inform decisions about whether to provide ATT in the homes of people with dementia. ATTILA is designed to answer questions about the efficacy and cost-effectiveness of ATT, with relevance for those who commission and provide care for people with dementia.

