#### Secondary objectives

(1) To establish whether these technologies can significantly *reduce the number of incidents* involving serious risks to safety and independent living, including acute admissions to hospital.

(2) *To reduce burden and stress* in family and other unpaid carers; and *increase quality of life* for people with dementia and their unpaid carers.

(3) To collect qualitative and quantitative data from people living with dementia, their paid and unpaid carers, and members of the NHS and CASSR teams about their *experience of using* these technologies.

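### In the first cost-effectiveness analysis, costs stop at entry to a care home or hospital with no permanence condition, while outcome days run to permanent institutionalisation

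*Protocol article*

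**What the plan says.** All references are to the protocol article.

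- **Cost-effectiveness, first analysis, cost side.** It will "measure costs only up to the point at which a study participant goes into a care home or hospital and not beyond". The article calls these community costs.
- **Cost-effectiveness, first analysis, outcome side.** The same sentence pairs them with the primary outcome, "days from randomisation to institutionalisation in the two year period". The result is meant to show the "incremental cost of community-based support for each additional institutional day avoided".
- **Time in days from randomisation to institutionalisation.** The endpoint is the "permanent transition of the individual from living in their own home to nursing or residential care home", or "admission to an acute care facility that results in permanent placement in a residential care or nursing home". Both limbs require permanence.
- **Cost-effectiveness, second analysis.** It will "measure costs for the whole 2-year period, including costs of care home and hospital stays", with EQ-5D change as the outcome.
- **Background and Secondary objectives.** ATT is claimed to "prevent unnecessary hospital admissions, and delay or prevent admission into residential or nursing care". One secondary objective is to reduce serious incidents, "including acute admissions to hospital".

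**The concern.** A cost per day gained is meaningful only if cost and days are accumulated over the same period for each participant. Here the outcome clock stops at a permanent move, whereas the cost clock as worded stops at entry to a care home or hospital of any kind. The closing words of the rule make it a stop, not a pause for the inpatient days, and nothing says that costing resumes after discharge.

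Take a participant who enters hospital on day 100, goes home on day 110 and moves permanently to a care home on day 600. The literal rule costs 100 days and credits 600. The 490 days at home after discharge (600 − 110) enter the denominator with no cost of ATT or community care in the numerator.

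Cost-effectiveness is one of the trial's two primary outcomes, and this analysis is to be run from both the health and social care perspective and the societal one. The mismatch need not cancel between arms. The arm with longer home time has more time in which a temporary stay can occur, and ATT is itself hypothesised to change hospital admissions.

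**Working it through.** **The passages side by side**

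| Event | Ends outcome days? | Ends costs, as worded? |
|---|---|---|
| Permanent move to a care home | Yes | Yes |
| Acute admission leading to permanent placement | Yes | Yes |
| Acute admission, then return home | No | Yes |
| Respite stay in a care home, then return home | No | Yes |

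The last two rows are the defect.

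**The plan's own figures.** The article gives no figure for the cost-effectiveness ratio. Its Sample size calculation section gives 50% against 35% institutionalised at two years and a mean gain of 55 days. The 55 reproduces with events accruing evenly: 0.15 × 730 / 2 = 54.75 days. The illustration below uses exponential times instead, because they allow a second event rate to be added. These give a larger gain of 66.5 days.

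**Inputs**
- From the article: 50% (control) and 35% (ATT) at T = 730 days.
- Assumed: exponential times; temporary entries at h per person-year, independent of institutionalisation; daily community cost of 50 (control) and 55 (ATT), in arbitrary units; no deaths.

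**Formulas**
- Daily institutionalisation rate: λ = −ln(1 − p)/730, that is −ln(0.50)/730 for control and −ln(0.65)/730 for ATT.
- Mean outcome window: (1 − exp(−λT))/λ. This gives 527 days (control) and 593 days (ATT), a difference of 66.5.
- Mean costed window under the literal rule: the same formula with λ + h/365 in place of λ.
- Cost per day gained: (55 × ATT costed days − 50 × control costed days) / 66.5.

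With matched windows: (55 × 593.1 − 50 × 526.6) / 66.5 = 94.6.

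| Temporary entries per person-year, control / ATT | Costed days, control (share of outcome window) | Costed days, ATT (share) | Difference in costed days | Cost per day gained |
|---|---|---|---|---|
| 0 / 0 | 527 (100%) | 593 (100%) | 66.5 | 94.6 |
| 0.25 / 0.25 | 426 (81%) | 475 (80%) | 48.8 | 72.4 |
| 0.5 / 0.5 | 352 (67%) | 388 (65%) | 36.4 | 56.5 |
| 1.0 / 1.0 | 253 (48%) | 274 (46%) | 21.2 | 36.5 |
| 0.5 / 0.375 | 352 (67%) | 428 (72%) | 76.6 | 89.8 |
| 0.5 / 0.625 | 352 (67%) | 353 (60%) | 1.6 | 27.8 |

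The outcome difference is 66.5 days in every row; only the costed days move. Combining the control window at 0.5 with the ATT window at 0.25 gives (55 × 475 − 50 × 352) / 66.5 = 8,525 / 66.5, about 128, which is above the matched value. So the bias can go either way. It also runs perversely: for a fixed control rate, ATT looks cheaper when it is followed by more temporary stays and dearer when it prevents them.

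**The case against.** The strongest reply is that the phrase is shorthand for the primary endpoint. That endpoint also has a care home limb and a hospital limb, and the same sentence names the primary outcome. The stated reason for having two analyses is that institutionalisation is itself partly resource use, which suggests a cut-off at institutionalisation and not at a short hospital stay. The Abstract continues assessments until institutionalisation or withdrawal, so service use is still recorded after a temporary stay. This reading is plausible, and under it the windows agree and only the wording is at fault. But the article does not state it. The same paragraph uses hospital stays in the general sense for the second analysis, and Background and Secondary objectives treat hospital admissions as separate from institutionalisation.

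A second reply is that costing detail belongs in a fuller document. That would answer a missing rule. Here a rule is stated, and it conflicts with the denominator it is paired with.

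Three stronger readings are tempting and not supported:
- *That the ratio will certainly be computed over mismatched windows.* The wording permits the shorthand reading, so this cannot be asserted.
- *That hospital savings drop out of the evaluation.* The second analysis includes hospital and care home stays over the full two years. The first is deliberately limited to community costs, so leaving inpatient cost out of it is a scope choice.
- *That a definite share of home days goes uncosted.* Any such figure rests on an assumed rate of temporary stays and on costs never resuming; the article gives neither.

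**Conclusion.** The rule as written is wrong for the ratio it feeds. The cost cut-off lacks the permanence condition that defines the outcome, so a temporary stay ends one clock and not the other. Neither the direction nor the size of the bias can be derived from the article. The windows coincide if there are no temporary stays. Under the assumed rates shown, the illustrative ratio moves from 94.6 to values between about 28 and 128; these figures show scale only and depend on exponential times, assumed entry rates and assumed daily costs. The defect is confined to the first cost-effectiveness analysis. Time to institutionalisation, the total-cost/EQ-5D analysis and the sample size are not affected.

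**What to change.** Amend the sentence so that costs and days both run from randomisation to one date: institutionalisation as defined for the primary outcome, death, or two years, whichever is first. State that community costs continue after discharge from a temporary hospital or care home stay. For the optional analyses at 24 and 52 weeks, replace two years by that horizon.

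State also whether the inpatient or respite cost of a temporary stay inside the window counts as a community cost. Either choice is defensible if it is declared and applied alike in both arms.

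The cost is one or two sentences. No new data are needed, since the modified CSRI already collects service use at the planned assessments. If shorthand for the primary endpoint was intended, a cross-reference to that definition settles the institutionalisation cut-off, with the treatment of temporary stays added.

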**Method/design:**

ATTILA (Assistive Technology and Telecare to maintain Independent Living At Home for People with Dementia) is a pragmatic, multi-centre, randomised controlled trial over 104 weeks that compares outcomes for people with dementia who receive ATT and those who receive equivalent community services but not ATT. The study hypothesis is that fewer people in the ATT group will go into institutional care over the 4-year period for which the study is funded. The study aims to recruit 500 participants, living in community settings, with dementia or significant cognitive impairment, who have recently been referred to social services.

Primary outcome measures are time in days from randomisation to institutionalisation and cost effectiveness. Secondary outcomes are caregiver burden, health-related quality of life in carers, number and severity of serious adverse events, and data on acceptability, applicability and reliability of ATT intervention packages. Assessments will be undertaken in weeks 0 (baseline), 12, 24, 52 and 104 or until institutionalisation or withdrawal of the participant from the trial.

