### Statistics

#### Sample size calculation

On average, 50% of participants with a BADLS score of >15 will enter residential care after 24 months
[44]. A reduction in the estimated 24-month transition to care home rate by 30% (i.e. 50% institutionalised at 2 years reduced to 35%) would require the involvement of 500 participants allowing for 10% attrition due to death while still living in a community setting. This equates to an average of 55 days of longer independent home life for participants receiving ATT. The trial would therefore be powered to detect a mean institutional delay of a little less than 8 weeks. Expert opinion suggests that 8 weeks is close to the minimum clinically important difference in delaying institutionalisation
[45].

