##### Handling of reports of death

It is likely that a substantial number of deaths may occur amongst participants who have been previously institutionalised and therefore will have met the primary outcome. For deaths among participants resident in the community, deaths that occur as a consequence of an identified risk that the ATT might have affected will be included as a secondary outcome measure (documented as a serious adverse event) and the number of identified un-related deaths in the two study groups will be compared in the overall analysis and included in a sensitivity analysis of the primary outcomes.

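### The first cost-effectiveness ratio measures days until institutionalisation but is described as a cost per institutional day avoided; the two agree only if days alive are equal between arms and home days end at death

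*Protocol article*

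**What the plan says.** The abstract of the protocol article makes cost-effectiveness a primary outcome: "Primary outcome measures are time in days from randomisation to institutionalisation and cost effectiveness".

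The Cost-effectiveness section describes two analyses. The first "will measure costs only up to the point at which a study participant goes into a care home or hospital and not beyond". It will then "examine cost-effectiveness in achieving the primary outcome (days from randomisation to institutionalisation in the two year period". The next sentence states what the ratio means: "This analysis will show the incremental cost of community-based support for each additional institutional day avoided".

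The event is defined under the heading for time to institutionalisation: "This is defined as the permanent transition of the individual from living in their own home to nursing or residential care home" (or an acute admission that ends in such a placement). Death is not part of it.

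Deaths are expected in both settings. The Sample size calculation gives 500 participants, "allowing for 10% attrition due to death while still living in a community setting". Handling of reports of death says: "It is likely that a substantial number of deaths may occur amongst participants who have been previously institutionalised". It also plans a sensitivity analysis of the primary outcomes for unrelated deaths among people still in the community.

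**The concern.** The denominator counts time before placement, while the label counts time spent in an institution. For one person these need not be mirror images over two years. Someone placed on day 300 who dies on day 400 has 300 days to institutionalisation. Subtracting from 730 implies 430 institutional days, but only 100 occurred. Someone who dies at home on day 200 has no institutional days and no time to institutionalisation.

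Commissioners are the intended readers, and they would take the ratio as the price of a care-home day saved. If home days gained exceed institutional days avoided, that price looks lower than it is. The label also has an awkward property: a death at home reduces institutional days, so it would count as a gain.

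**Working it through.** **The plan's own figure.** The Sample size calculation gives a mean gain of 55 days. Spreading the events evenly over 730 days gives (0.50 − 0.35) × 730 / 2 = 54.75, so it reproduces. That calculation contains no deaths, and without deaths the two quantities are identical.

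**The identity.** In each arm, mean home days + institutional days + days dead = 730, where home means alive and not permanently institutionalised. Subtracting control from ATT:

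home days gained − institutional days avoided = difference in mean days alive (ATT − control).

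Deaths alone therefore do not separate the two. A difference in days alive does, and so does a day count that does not stop at death.

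**Inputs from the protocol.** 50% (control) and 35% (ATT) institutionalised at two years; 10% dying in the community.

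**Assumptions.** Constant hazards; one community-death hazard for both arms, set to give 10% deaths in control; post-placement mortality varied, because the article gives no rate.

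**Hazards.**
- Control: 1 − 0.50 − 0.10 = 0.40 remain at home at two years, so the total hazard is −ln(0.40)/2 = 0.458 per year. Split 5:1, this is 0.382 for institutionalisation and 0.076 for death at home.
- ATT: the death hazard stays at 0.076. The institutionalisation hazard that gives 35% is 0.235, so the total is 0.311. Community deaths come out at 11.4%.

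**Home days ended at death**, (1 − e^(−aT))/a, with a the total hazard and T two years: control 478.0, ATT 543.3, gain 65.3.

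**Days with home deaths censored**, (1 − e^(−λT))/λ, with λ the institutionalisation hazard: gain 71.9. This describes a world without death.

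**Institutional days**, λ/(a − μ) × [(1 − e^(−μT))/μ − (1 − e^(−aT))/a], with μ the post-placement death hazard. For a given incremental cost, the understatement is 1 − (institutional days avoided / days used as denominator).

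| Post-placement mortality | Institutional days avoided | Understatement, count ended at death (65.3) | Understatement, deaths censored (71.9) |
|---|---|---|---|
| same hazard as at home | 65.3 | 0% | 9% |
| 10% per year | 63.9 | 2% | 11% |
| 20% per year | 58.8 | 10% | 18% |
| 30% per year | 53.8 | 18% | 25% |
| 40% per year | 48.7 | 25% | 32% |

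**Sensitivity to calibration.** Reading 50% and 35% as risks in the absence of death, with a common death rate, gives 60.6 home days gained and 60.6 institutional days avoided. Post-placement hazards of 1.5, 2 and 3 times the home hazard then give 59.0, 57.5 and 54.6 institutional days avoided, which is 3%, 5% and 10% fewer.

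**Mortality differing by arm** (same calibration, equal mortality by place). An ATT death hazard ratio of 0.8 gives 68.1 home days gained against 58.2 institutional days avoided. A ratio of 1.2 gives 53.3 against 63.0. The direction can therefore reverse.

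**The case against.** The strongest reply is that this is one loose sentence. The effect measure is explicit, and the Sample size calculation describes the same gain as extra time living at home, so the intended meaning can be recovered. How deaths are scored may be settled in a full protocol or health-economic plan that is not shown. The second analysis covers total costs, including care-home stays, so commissioners would have more than this ratio.

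Much of that stands. The absence of a scoring rule for deaths is not the point here. But the article states both the denominator and its interpretation, and a later scoring rule would not make the published interpretation match the measure. The sensitivity analysis for deaths concerns people still in the community. It does not address deaths after placement, which drive the gap in the table when mortality is higher there.

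A reader might infer three stronger things that the documents do not support:
- **That expected deaths by themselves make the ratio wrong.** They do not: under equal mortality the figures are 65.3 and 65.3. The person-level examples can cancel in a difference between arm means.
- **That a stated result is in error.** No numerical ratio is given, so the fault is in the labelling.
- **That the understatement is about 10% to 31%.** That follows from fixing community deaths at 10% in both arms (71.5 home days gained against 64.4 to 49.0 institutional days avoided). It builds in an ATT community-death hazard of 0.066 against 0.076 per year, 13% lower, which the protocol does not claim.

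**Conclusion.** The concern holds as a mismatch between the effect measure and the interpretation given to a primary-outcome ratio. Followed as written, the plan would report one quantity under another's name. The size is not fixed by the protocol. It is zero if mortality is equal by place and arm and home days end at death. It is about 2% to 25% if post-placement mortality is 10% to 40% per year, and about 9% to 32% if home deaths are censored. The upper end is an assumption, since 40% per year is about 6.7 times the control hazard of death at home. The direction, a cost per institutional day avoided that looks too low, holds when mortality is higher after placement or home deaths are censored, with mortality otherwise equal between arms. It can reverse if ATT raises mortality. The identity itself needs no distributional assumption; the percentages rest on constant hazards and a common community-death hazard.

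**What to change.** In the Cost-effectiveness section:

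1. Define the effect of the first analysis as days alive and not permanently institutionalised, from randomisation to day 730, with a death at home ending the count on the day of death.
2. Describe the ratio as the incremental community cost per additional day lived at home.
3. If a cost per institutional day avoided is also wanted, compute institutional days directly from placement and death dates, and report it separately with deaths by arm beside it.

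The cost is a change of wording and a small change to the derivation. Placement dates are needed for the primary outcome anyway, and dates of death are needed to end the count. The downside is that the first ratio can no longer be presented as a saving in institutional days.

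### The total-cost analysis names EQ-5D change over 2 years as its effect measure, which is not observed for participants who die; the already planned QALY should be the named measure

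*Protocol article*

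**What the plan says.** The abstract (Method/design) gives cost-effectiveness primary status: "Primary outcome measures are time in days from randomisation to institutionalisation and cost effectiveness".

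The Cost-effectiveness section then sets out two analyses. The point concerns the second. On the cost side, "The second type of analysis will measure costs for the whole 2-year period, including costs of care home and hospital stays". On the effect side, it "will then examine cost-effectiveness where the outcome is EQ-5D change, also over the 2-year period". The next sentence reads "We will also use the EQ-5D to generate Quality-Adjusted Life Year (QALY) measures by attaching societal weights". The section does not say which of the two EQ-5D measures governs if they disagree.

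On the decision summary, "We will compute incremental cost-effectiveness ratios and plot cost-effectiveness acceptability curves". The curves come from the net benefit approach with bootstrap regression, for whichever outcomes correspond.

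Deaths are foreseen in two places. The sample size is calculated "allowing for 10% attrition due to death while still living in a community setting". The section on reports of death adds: "It is likely that a substantial number of deaths may occur amongst participants who have been previously institutionalised". Unrelated deaths among community residents are to be compared between arms and "included in a sensitivity analysis of the primary outcomes". The Analyses section commits to intention to treat with every randomised participant.

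**The concern.** A change over 2 years needs a value at 2 years. Participants who die have none unless the plan assigns one, and the article assigns none to this measure. Their costs do exist up to death. The measure named as the outcome of a primary analysis is therefore undefined for a group that the protocol itself expects to be sizeable.

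Survival is a post-randomisation event. The article allows that the intervention could affect it, because it treats separately those deaths linked to a risk that the technology might have influenced. An effect measure that conditions on survival no longer compares the randomised groups. It also leaves out the largest possible loss of health. The result is meant to inform whether councils go on investing in the technology, so the lead effect measure should be one that registers death.

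**Working it through.** The article gives no figure for this analysis, so there is none to reproduce. The check asks what each candidate measure shows when the arms differ in mortality only.

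**Inputs from the protocol**
- Horizon of 2 years, with visits at weeks 0, 12, 24, 52 and 104.
- 10% deaths in the community, or 0.10 × 500 = 50 participants. Deaths after institutionalisation come on top, with no figure given.

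**Inputs assumed here (not in the documents)**
- Utility falls linearly from 0.60 to 0.50 over 2 years in both arms, so u(s) = 0.60 − 0.05s.
- Time of death T is uniform on 0 to 2 years, so E[T] = 1 and E[T²] = 4/3.
- 2-year mortality is 20% in one arm and 25% in the other.
- Care costs 15,000 to 30,000 per person-year.

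**EQ-5D change in survivors**
- Each arm: 0.50 − 0.60 = −0.10. Difference between arms: 0.

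**QALY with utility 0 from death**
- Survivor: 2 × 0.55 = 1.10.
- Participant who dies: E[0.60T − 0.025T²] = 0.60 − 0.025 × 4/3 = 0.567.
- Arm with 20% deaths: 0.80 × 1.10 + 0.20 × 0.567 = 0.993.
- Arm with 25% deaths: 0.75 × 1.10 + 0.25 × 0.567 = 0.967.
- Difference: −0.05 × (1.10 − 0.567) = −0.027 QALY per participant.

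**EQ-5D change with death scored 0**
- 20% deaths: 0.80 × (−0.10) + 0.20 × (−0.60) = −0.200.
- 25% deaths: 0.75 × (−0.10) + 0.25 × (−0.60) = −0.225.
- Difference: −0.025.

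**Cost side, by how the deceased are treated**
- Everyone's costs counted, effect in survivors only: the arm with more deaths has 0.05 × 1 = 0.05 fewer person-years to cost, which is 750 to 1,500 less per participant, against an effect difference of 0.
- Person-level net benefit with no value for the deceased: they leave both sides. Costs and effects both come from survivors, and both differences are 0 under these inputs.

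**Range over the assumptions** (effect difference for the arm with more deaths)

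| Excess mortality | Utility path | Survivor change | QALY |
|---|---|---|---|
| 0 points | either | 0 | 0 |
| 5 points | flat at 0.60 | 0 | −0.03 |
| 5 points | 0.60 to 0.50 | 0 | −0.027 |
| 10 points | flat at 0.60 | 0 | −0.06 |
| 10 points | 0.60 to 0.50 | 0 | −0.053 |

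With a flat path the survivor QALY is 1.20 and that of a participant who dies is 0.60, so each percentage point of excess mortality costs 0.006 QALY. With the falling path it costs 0.00533.

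**The case against.** The strongest reply is that the remedy is already in the plan. QALYs will be generated from the same data, ratios and curves are planned for the corresponding outcomes, and a mortality difference would show in the QALY result. This stands. What remains is the choice of lead measure: the article names the unsuitable one as the outcome and gives the suitable one no priority.

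Second, the article does not say that EQ-5D change is computed in survivors only. With death scored 0, a change can be given to everyone, and it then shows a loss (−0.025 above). This also stands, so the point is conditional on no such value being assigned. However, the article mentions societal weights only in the QALY sentence. A change score with death at 0 would also treat an early and a late death alike, which a QALY does not.

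Third, deaths are to enter a sensitivity analysis of the primary outcomes. That covers unrelated deaths in the community, not those after institutionalisation, and it does not alter the main measure.

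Fourth, rules for deaths may sit in an analysis plan that is not shown. That is fair, and the absence of such rules is not the point. The choice of measure is made in this document.

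Two stronger readings are tempting. A reader might infer that an arm with more deaths will look cheaper with no loss of effect. The documents do not fix this. It needs survivor-only effects set against everyone's costs, whereas the planned net benefit regression, if run on individuals, needs a cost and an effect for the same person and would more likely drop the deceased from both. A reader might also infer that a change over 2 years discards the intermediate visits. The text does not say so: it plans repeated measures regression for continuous outcomes and allows economic analyses at 24 and 52 weeks.

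**Conclusion.** The point holds as an improvement to the choice of measure. EQ-5D change over 2 years is a poor effect measure for a total-cost analysis in a population with expected deaths. Unless a value is assigned at death, it conditions on survival and cannot show the effect of a mortality difference, whichever way the deceased are handled on the cost side. The planned QALY can.

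The size depends on assumptions. For 5 to 10 points of excess mortality and the utilities used here, the unseen loss is about 0.027 to 0.06 QALY per participant. The documents give no difference in mortality between arms and no utility values. With equal mortality and equal utility paths, nothing is lost. The text does not support saying that the trial as planned would conceal a mortality difference, because the QALY result is to be produced as well.

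**What to change.** In the Cost-effectiveness section, name the QALY over 104 weeks as the effect measure of the total-cost analysis. Define it as the area under the EQ-5D utility values at weeks 0, 12, 24, 52 and 104, with utility 0 from the date of death, in all randomised participants. Report EQ-5D change as a supportive description in survivors, labelled as such, without its own incremental ratio.

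The instrument, the visits and the QALY derivation are already planned, so the change is mainly one of wording. It is not entirely free. QALYs need interpolation between visits, and imputation where EQ-5D is missing. The abstract suggests that assessments may end at institutionalisation, and the design rates put 35% to 50% of participants there by 2 years. If EQ-5D does stop at that point, later utilities must be collected or imputed. EQ-5D change at 2 years would face the same gap, so this is no reason to prefer it.
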